#### Accuracy and validity assessment

The unit of analysis is intervention rather than patient because each patient can have multiple interventions. Validity will be measured by the sensitivity and specificity of the data acquisition process. The sensitivity corresponds to the proportion of correctly identified interventions by Assessor 1, among the interventions identified by Assessor 2 (reference standard). The specificity is computed on the patients with no interventions (as measured by Assessor 2) by using the number of patients with no interventions identified by Assessor 1. The confidence intervals will be calculated for both sensitivity and specificity using robust standard errors, through a logistic regression fitted with a generalized estimating equation (GEE) to take into account clustering by center and patient (due to the limitations of the software, each clustering level will be considered in separate models and both confidence intervals will be reported). Additionally, the percentage of patients with the correct number of VA interventions within 6 months, as identified by Assessor 1, will be presented as a measure of accuracy, together with the Cohen’s weighted kappa as the degree of agreement for the number of VA interventions per patient, reported by the two assessors. The 95% confidence intervals for the accuracy and kappa statistics will be computed by bootstrap stratified by center.

Several subgroup analyses will be conducted to investigate variability of these measures according to patients’ and centers’ characteristics. Any tests comparing measures of validity across subgroups will be performed with a logistic model, using GEE to take into account the clustering of the data by patient and center.

Accuracy of rate of vascular access interventions, time to first intervention (allowing for imprecision of +/− 3 days) and type of vascular access will also be analyzed. For the first two continuous outcomes, the accuracy of the data will be reported as the percentage of correct information collected by Assessor 1. Finally, the accuracy of type of intervention collected by Assessor 1 will be reported as the percentage of type of intervention correctly identified and the Cohen’s kappa will be presented as a measure of agreement between the two assessors. All the measures of accuracy will be presented with 95% confidence intervals.

All data will be analyzed using R software. The script for the statistical analysis is provided as Supplementary Item S4.

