### Statistical considerations

#### Sample size calculation

The sample size has been calculated for the sensitivity, i.e. the proportion of interventions correctly identified by Assessor 1 and specificity, i.e. the proportion of patients with no interventions recorded by Assessor 1 that do not have a record of interventions.

Assuming an event rate of 2 vascular access interventions/ patient-year based on recent data from a study collecting a comparable range of vascular access interventions in HD patients [28], the overall expected number of interventions over a 6 month period will be equal to the number of participants, although there will be patients with no intervention and patients with more than one intervention. Assuming a true sensitivity of 90%, 520 records of interventions will provide an approximate 5% width for the 95% confidence interval.

With the rate of 2 vascular access interventions/ patient-year and assuming a Poisson distribution, the expected number of patients without an intervention in the 6 months is 193. This number will allow the calculation of the specificity with a 10% width for the 95% confidence interval, assuming a true specificity of 90%.

The sample size will be inflated to account for 15% potential dropouts (i.e. early study exit). This corresponds to a final sample size of 612 patients.

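### Subgroup differences in percent-correct count can reflect how many interventions patients have and not how accurately staff record them

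*Protocol article*

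**What the plan says.** Under Accuracy and validity assessment, the protocol article defines validity by two measures: sensitivity, per intervention, and specificity, among patients for whom Assessor 2 found none. It then adds two patient-level summaries: "the percentage of patients with the correct number of VA interventions within 6 months" and Cohen's "weighted kappa as the degree of agreement for the number of VA interventions per patient". The next paragraph opens with "Several subgroup analyses will be conducted to investigate variability of these measures according to" patient and center characteristics. On its natural reading this takes in all four measures. The sentence after it, on formal tests, is narrower: it specifies logistic GEE models for comparing validity measures.

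The correct total per patient is not a side measure. Under Primary outcome measures it is one of the two parts of the definition of accuracy. Nothing in the article relates percent-correct or kappa to the reference count when subgroups are compared.

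**The concern.** A patient with no interventions can be misclassified only by a false record. A patient with three gives the assessor three chances to miss one. Percent-correct therefore depends on the count distribution of the group as well as on the assessor. Kappa depends on the spread of the counts too.

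Intervention frequency may well differ between subgroups here. Sites were chosen to vary in location, size, modality and setting, and Table 2 lists different procedures for AVF/AVG and for CVC. The Discussion treats frequency across settings and countries as something the study will determine. Length of follow-up also matters: data collection stops at death, transfer or change of therapy, and a group with more early exits accrues fewer interventions per patient. At stake is how the results by setting are read. A unit type could look less accurate only because its patients have more procedures.

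**Working it through.** **Inputs from Sample size calculation.** Rate: "Assuming an event rate of 2 vascular access interventions/ patient-year based on recent data", so a mean of 1 per patient in 6 months. Counts: "assuming a Poisson distribution, the expected number of patients without an intervention in the 6 months is 193". Sensitivity: "Assuming a true sensitivity of 90%, 520 records of interventions will provide an approximate 5% width for the 95% confidence interval". Specificity: "specificity with a 10% width for the 95% confidence interval, assuming a true specificity of 90". Dropout: "The sample size will be inflated to account for 15% potential dropouts (i.e. early study exit").

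**The plan's own figures.**
- Width for sensitivity: 2 × 1.96 × √(0.9 × 0.1/520) = 5.2%. Agrees with about 5%.
- Patients with none: 520 × e⁻¹ = 191, against 193. Close enough.
- Width for specificity with 193 patients: 2 × 1.96 × √(0.9 × 0.1/193) = 8.5%, inside the stated 10%.
- 520/0.85 = 611.8, so 612. Reproduces.

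**Model.** Let the true count be Poisson with mean m per 6 months. Each intervention is recorded with probability 0.9, so missed interventions are Poisson with mean a = 0.1m. False records are Poisson with mean b = −ln 0.9 = 0.105, which gives 90% specificity. The recorded total is right when the number missed equals the number of false records:

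P(correct) = e^−(a+b) × Σₓ (ab)ˣ/(x!)²

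For m = 0.5: e^−0.1554 × (1 + 0.0053 + …) = 0.8561 × 1.0053 = 0.861. For m = 1.5: e^−0.2554 × (1 + 0.0158 + …) = 0.7746 × 1.0159 = 0.787.

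**Percent-correct with identical assessors in both groups** (the subgroup rates are assumptions; each pair averages the planned 1 per 6 months):

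| Rates per 6 months | With false records | No false records, e^(−0.1m) |
|---|---|---|
| 0.5 v 1.5 | 86.1% v 78.7% | 95.1% v 86.1% |
| 0.75 v 1.25 | 84.2% v 80.5% | 92.8% v 88.2% |
| 0.9 v 1.1 | 83.0% v 81.6% | 91.4% v 89.6% |

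If false records occur only in patients with no true intervention, the first row is 89.1% v 83.8%. The gap at 0.5 v 1.5 is thus about 5 to 9 points, depending on the false-record model. Over the wider range 0.25 to 3 per 6 months, percent-correct falls from 88.0% to 68.8% with false records.

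By true count, the probability of a correct total with false records is 90%, 82%, 75% and 68% for 0, 1, 2 and 3 interventions, whatever the group's rate. All of the crude difference comes from the mix of counts.

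**Follow-up.** At 2 per patient-year, patients followed for 3 months expect 0.5 interventions and those followed for 6 months expect 1. With no false records, percent-correct is 95.1% v 90.5% from that alone.

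**Weighted kappa**, 1 − Σd·p/Σd·r·c, where p is the joint proportion, r and c are the margins, and d = |i − j| (linear) or (i − j)² (quadratic):

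| Mean per 6 months | 0.25 | 1 | 2 | 3 |
|---|---|---|---|---|
| Linear, false records | 0.72 | 0.82 | 0.82 | 0.81 |
| Linear, none | 0.935 | 0.902 | 0.867 | 0.840 |
| Quadratic, false records | 0.77 | 0.90 | 0.92 | 0.92 |
| Quadratic, none | 0.946 | 0.942 | 0.938 | 0.933 |

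**Sensitivity.** A simulated two-proportion test without clustering, at 1 v 4 interventions per patient-year and 260 patients per group with equal accuracy, rejected in 5.1% of runs. The rate does not distort it.

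**The case against.** A reader might infer that the plan will declare significant accuracy differences between equally accurate units. If percent-correct were tested with 260 patients per group, equal assessors would differ significantly in about 60% of studies at 0.5 v 1.5 (95% with no false records). The article plans no such test. Its sentence on formal tests concerns validity, which the same section defines as sensitivity and specificity. The figure also depends on the assumed contrast: it is 20% or 42% at 0.75 v 1.25, and 7% or 11% at 0.9 v 1.1. This objection stands in full.

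A reader might also infer that percent-correct and kappa will point in opposite directions. That is not general. With no false records, linear kappa falls along with percent-correct; with false records the contrast comes mainly from the lowest-rate group; and the article states no weights.

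Third, dependence on the rate is not in itself an error. How often a patient's total is right in a given setting is a real property of the outcome measure there, and users of the measure may want it. This stands as a reason to keep the crude figure and not to bar subgroup kappa. It does not make the crude figure a comparison of recording accuracy.

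Last, the analysis plan is in Supplementary Item S4, which is not shown, and may stratify. Subgroup definitions and table layouts can be left there. But the article itself commits to examining how these measures vary across subgroups and to presenting all accuracy measures with 95% confidence intervals, so a reader of the article needs to know what a difference means.

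**Conclusion.** The point holds for the descriptive subgroup reading of percent-correct and, less predictably, of weighted kappa. With the plan's own accuracy values and Poisson counts, equally accurate groups differ on percent-correct by about 7 points at 0.5 v 1.5 interventions per 6 months, 4 points at 0.75 v 1.25, and 1 point at 0.9 v 1.1. It matters only if subgroups differ materially in intervention frequency or follow-up, and the article gives no subgroup rates. For kappa, neither size nor direction can be stated without the weights and the false-record rate. Sensitivity, specificity and the formal tests worded around them are not affected.

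**What to change.** In Accuracy and validity assessment, state that subgroup conclusions about recording accuracy rest on sensitivity and specificity. For subgroups, present percent-correct by Assessor 2 count (0, 1, 2 or more), or standardised to the overall distribution of Assessor 2 counts, next to the crude value. Show any subgroup kappa together with that subgroup's intervention rate.

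Standardising means Σ wₖ·pₖ, where wₖ is the overall share of patients with count k and pₖ the subgroup's percent-correct at that count. In the model above, two equal-sized groups at 0.5 and 1.5 per 6 months have overall shares of 41.5%, 31.9% and 26.6% for 0, 1 and 2 or more. The group values are 90.0%, 81.9% and 73.4% v 90.0%, 81.9% and 70.5%. The standardised results are 83.0% v 82.2%, so the artefact shrinks from 7.4 to 0.8 points.

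No new data are needed; the cost is a sentence or two and a few lines of code. The downside is that small count strata must be merged, which leaves a residual such as the 0.8 points above.

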**Methods:**

VALID is a prospective, multi-center, multinational validation study that will assess the accuracy and feasibility of measuring VA function, defined as the need for interventions to enable and maintain the use of a VA for HD.

The primary objective is to determine whether VA function can be measured accurately by clinical staff as part of routine clinical practice (Assessor 1) compared to the reference standard of documented VA procedures collected by a VA expert (Assessor 2) during a 6-month follow-up period. Secondary outcomes include feasibility and acceptability of measuring VA function and the time to, rate of, and type of VA interventions.

An estimated 612 participants will be recruited from approximately 10 dialysis units of different size, type (home-, in-center and satellite), governance (private versus public), and location (rural versus urban) across Australia, Canada, Europe, and Malaysia.

Validity will be measured by the sensitivity and specificity of the data acquisition process. The sensitivity corresponds to the proportion of correctly identified interventions by Assessor 1, among the interventions identified by Assessor 2 (reference standard). The feasibility of measuring VA function will be assessed by the average data collection time, data completeness, feasibility questionnaires and semi-structured interviews on key feasibility aspects with the assessors.

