
While vascular access interventions have been reported in HD research and collected by renal registries [22–27] the granularity of data collection (i.e., type of vascular access interventions, date of intervention, and indication of intervention) vary substantially across studies and registries precluding reliable comparisons across trials and countries to inform research and clinical practice. A Canadian experience including five Canadian dialysis programs has shown that granular data collection of all types, dates, and indications of vascular access interventions in patients on HD using the Dialysis Measurement Analysis and Reporting (DMAR) system is feasible and reliable [22, 27, 28]. However, it remains unknown whether these data can be collected in other countries and different settings (i.e., in-center versus satellite versus home-based HD; rural versus urban; private versus public; small versus large units) by clinical staff without special expertise in vascular access and as part of routine clinical practice. VALID will address this uncertainty by assessing the validity, acceptability and feasibility of measuring vascular access function, defined by the need for interventions to enable and maintain the use of a vascular access for HD, by clinical staff as part of their routine clinical practice in a prospective, multi-center, multinational validation study covering a broad range of HD settings to ensure successful implementation of this core outcome measure in research and clinical practice without the need for additional resources or expertise in vascular access [21].

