### Study design and setting

VALID is a prospective, multi-center, multinational validation study that will assess the accuracy and feasibility of measuring vascular access function in patients undergoing maintenance HD by clinical staff as part of routine clinical practice in 10 HD centers across 7 countries (Australia, Canada, France, Malaysia, the Netherlands, Switzerland, and the United Kingdom). The study schema is displayed in Fig. 1. Study sites have been purposefully selected to capture a broad range of different HD settings including geographical location (international sites, rural/remote and urban HD units), unit size (small to large HD units), HD modality (in-center-, satellite, home-based HD) and setting (private versus public hospital).

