#### Feasibility assessment

Time required for measuring vascular access function will be reported as study participant mean with standard deviations or median with interquartile range (IQR) depending on the distribution. Any subgroup comparison will be performed with linear models fitted with GEE with clustering by center.

The feasibility questionnaire will be analyzed quantitatively by mean, median, and percentage of assessors rating feasibility aspects as feasible (4–5 points on Likert scale) and qualitatively by thematic analysis if sufficient comments are provided.

The transcripts of the semi-structured interviews with Assessors 1 and 2 on feasibility aspects of data collection will be imported into HyperRESEARCH (ResearchWare, USA) and analyzed thematically. Thematic analysis involves identifying, examining, coding, comparing and grouping concepts to develop themes that describe the phenomenon being investigated and addresses the research question [34]. Using thematic analysis, the Chief Principal Investigator will code the transcript line-by-line to identify concepts relevant to the assessors’ perspectives on the feasibility of measuring vascular access function as part of routine clinical practice and for research purposes. The preliminary codes will then be reviewed by co-investigators who will independently read the transcripts and discuss any feedback with the chief investigator. This form of investigator triangulation can enhance the analytical framework and ensure that the full range and depth of data are captured in the initial analysis.

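### With 10 centers, an uncorrected robust GEE test is too liberal for subgroup factors that are properties of whole centers

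*Protocol article*

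**What the plan says.** Under Accuracy and validity assessment, the article announces that "Several subgroup analyses will be conducted to investigate variability of these measures according to patients’ and centers’ characteristics". It then names the method: "Any tests comparing measures of validity across subgroups will be performed with a logistic model, using GEE to take into account the clustering", with patient and center given as the clustering levels.

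A few lines earlier, for the confidence intervals of overall sensitivity and specificity, the same section specifies a logistic GEE with robust standard errors. It explains that, because of a software limitation, "each clustering level will be considered in separate models" and both intervals are reported. It does not say which of the two models supplies the p-value of a subgroup test.

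Under Feasibility assessment, for the time needed to collect the data: "Any subgroup comparison will be performed with linear models fitted with GEE with clustering by center".

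The study runs "in 10 HD centers across 7 countries" (Study design and setting; the abstract says approximately 10 units). The Background lists the settings of interest, among them "rural versus urban; private versus public; small versus large units".

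The article gives no significance level for the subgroup tests, no number of centers per subgroup, no ICC and no small-sample correction. The analysis script and analysis plan are in Supplementary Item S4, which is not available here.

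**The concern.** A factor that is constant within a center can be compared only between centers. For rural versus urban, the independent information is 10 centers, however many interventions they record. Each of the two models the article allows has a weakness here:

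- **Clustered by center.** The sandwich variance relies on having many clusters. With 10 clusters split into two small groups it is too small on average and unstable, and a normal reference distribution ignores both faults.
- **Clustered by patient.** Correlation between patients of the same center is left out, so the standard error is too small whenever centers truly differ. Some difference is plausible. According to the Index test section, a local staff member collects the data by local practice, either as events occur or retrospectively, so rater and data source are largely shared within a center.

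The sites were chosen to span settings. A chance finding that accuracy depends on setting would bear on whether the measure is thought fit for general use.

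**Working it through.** **Step 1. The article's own figures.**
- Sample size: 520 / 0.85 = 611.8, so 612, as stated.
- Sensitivity interval: 2 × 1.96 × √(0.9 × 0.1 / 520) = 5.2%, against about 5% stated.
- Patients without an intervention: 520 × e⁻¹ = 191, against 193 stated.
- Specificity interval: 2 × 1.96 × √(0.9 × 0.1 / 193) = 8.5%, within the 10% stated.

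The inputs 520 interventions, 90% sensitivity and 10 centers are therefore usable. The article states no error rate for the subgroup tests.

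**Step 2. Patient clustering, by hand.** With 520 / 10 = 52 interventions per center, ignoring center correlation understates the variance of a center-level contrast by about 1 + (52 − 1) × ICC. The false-positive rate is then about P(|Z| > 1.96 / √that factor).

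| ICC (assumed) | Factor | 1.96 / √factor | False positives |
|---|---|---|---|
| 0 | 1.00 | 1.96 | 5% |
| 0.02 | 2.02 | 1.379 | 17% |
| 0.05 | 3.55 | 1.040 | 30% |
| 0.10 | 6.10 | 0.794 | 43% |

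**Step 3. Center clustering, by hand, for equal-sized centers split 5/5.** The uncorrected sandwich divides each group's sum of squared center deviations by 5² where an unbiased variance divides by 5 × 4, so it is 4/5 of what it should be. Treating center means as normal, the test rejects when |t₈| > 1.96 × √0.8 = 1.753. That has probability 11.8% whatever the ICC. The argument uses only center means, so it holds equally for a linear GEE on time.

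**Step 4. Simulation with no true difference.** Inputs: 10 centers, about 520 patients with Poisson(1) interventions each, sensitivity 90%, beta-distributed center effects, patient-level correlation 0.1, center sizes equal or varying (coefficient of variation 0.5), two-sided 5%, 3,000 runs per setting. Ranges are over ICC 0 to 0.10 for the center-clustered and corrected tests, and over ICC 0.02 to 0.10 for patient clustering.

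| Centers per group | Center-clustered z | Patient-clustered z | Mancl-DeRouen with t₈ | t test on center proportions |
|---|---|---|---|---|
| 5/5 | 10.2-18.5% | 17.6-42.5% | 2.4-4.6% | 4.2-5.4% |
| 4/6 | 11.7-18.0% | 15.0-41.9% | 3.3-4.6% | 3.7-5.3% |
| 3/7 | 14.8-20.9% | 15.4-40.2% | 4.2-5.4% | 3.6-5.1% |
| 2/8 | 23.1-28.4% | 16.8-37.5% | 5.9-8.7% | 4.5-5.9% |

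At ICC 0 the patient-clustered test rejects 4.6-5.0% of the time for these splits. If one group has a single center, the center-clustered test rejects in 55-59% of runs and neither remedy gives a useful result.

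**Step 5. Cross-checks.**
- Including further runs with an exchangeable working correlation, the center-clustered range for 2/8 is 23-29%.
- With 193 records, as for specificity, center clustering gives 10-17% for 5/5 to 3/7 and 18-23% for 2/8.
- With 100 centers the center-clustered rate is 5.7%, so the excess comes from having few centers.
- A factor that varies within centers gave 10.9% under center clustering (ICC 0.05).

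**The case against.** The article names neither a Wald test nor a reference distribution. It states robust standard errors only for the confidence intervals, and the choice of correction could sit in Supplementary Item S4. This stands as a limit: the document does not prove that an uncorrected test will be run. It does not remove the point, because the method as described leads to that test unless something is added.

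A reader might infer that the subgroup sentence promises joint clustering by patient and center, which the software cannot do. The text does not compel that reading. The confidence-interval sentence uses parallel wording and explains that it means separate models, and the subgroup sentence can follow the same convention. What remains open is which model gives the p-value.

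A reader might also quote a single inflated error rate, such as 40%, as a property of the plan. The documents do not support that. They give no ICC, center sizes or subgroup composition, and the 40% end needs both a patient-only p-value and an ICC of 0.10.

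Finally, not every subgroup factor is a whole-center factor. Hemodialysis setting is recorded per patient and may vary within a center. The comparisons are described as exploring variability, with no decision rule attached. Both points narrow the scope, and both are accepted.

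**Conclusion.** The point holds for center-level factors. An ordinary robust z test at 5% with 10 centers gives roughly 10-20% false positives for a 5/5 or 3/7 split and 23-29% for 2/8 when clustered by center, and it is at least about 10% at every ICC tried. Clustered by patient only, it depends on between-center variation: about 5% with none, 15-18% at ICC 0.02 and about 40% at ICC 0.10.

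These figures rest on an assumed z test, 5% level, split, ICC and center-size pattern. The weakness extends to the center-clustered linear GEE for collection time, where the 5/5 calculation applies directly.

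It would be wrong to infer that the main results are compromised. The subgroup comparisons are secondary, and the point estimates of overall sensitivity and specificity do not change. The change is worth making before the data are analyzed.

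**What to change.** For any characteristic that is constant within a center:

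1. Take the p-value and confidence interval only from the center-clustered model, with a small-sample-corrected sandwich variance (for example Mancl-DeRouen) and a t distribution on (centers − 2) degrees of freedom, which is 8 here. A t test on center-level proportions or a permutation of center labels is an alternative.
2. Report the number of centers in each subgroup, and treat results as descriptive where a group has very few. Even the corrected sandwich runs at about 6-9% for 2/8. Where exactly to draw that line is a matter of judgement.
3. Apply the same correction to the center-clustered linear GEE for collection time.

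If Supplementary Item S4 already contains such a correction, a sentence in the article saying so is enough.

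The cost is a change of wording and of analysis code, with no new data. Intervals will be wider, and fewer subgroup differences will reach nominal significance.
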